### Part 1: evaluating the effectiveness of SFL-research design

#### Overview

Phase one of SFL encompassed the first delivery of the programme in Sheds. Following assessment of the implementation environment, namely the capacity and resource constraints of provider organisations to deliver SFL along with the nuances, ethos and autonomy of the inner (Sheds) setting, the SFL 10-week intervention was implemented on a phased basis across two cohorts comprising two counties in each cohort with a view to delivering Phase 2 as a single cohort across a further four new counties (i.e. Phase 1 (4 counties, two cohorts); Phase 2 (4 counties, one cohort); see participants and sampling). A mixed methods approach was applied to assess the impact of SFL Phase 1 testing on the biopsychosocial health of participants up to 12 months. This consisted of focus groups, interviews and questionnaires assessing health outcomes.

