#### Participants and sampling

Respecting the autonomous and informal environment of the Sheds is an important factor in delivering health promotion through Sheds [27, 33]. Therefore, Sheds are recruited to participate in the SFL programme and evaluation via purposive sampling using an expression of interest process with the objective to deliver SFL in a diverse range of Shed settings (small/large, urban/rural). All adult males in the Sheds setting were eligible to participate in the study providing they had good proficiency of the English language and could give informed consent. A sample size estimation was undertaken using G*Power 3.1.9.2 software using physical activity (PA) as the key outcome measure, whereby it was calculated that 106 participants would be required for a trial in which participants were individually randomised (the decision to use PA as the primary outcome measure was determined through consultation with Shedders who requested that PA be a key focus of SFL during the initial pilot phase). However a clustered design in which SFL was delivered to small clusters of men within Sheds was more preferable to honour the Shed ethos whilst also ensuring a wide geographical spread. For this reason a design with circa 20 men in each cluster was estimated. A previous study with middle-aged men suggested that this design effect is ~ 2.4, thus increasing the sample size required to 255 [47]. Allowing for a 20% dropout based on a sample size estimation, the final total required was 306 or 15 clusters. In the event of low participation within clusters, it was decided that SFL would be targeted at clusters with similar representation. In Phase 1, 421 Shedders participated across 22 clusters and these were divided into two cohorts. Whilst delivery occurred in the first cohort (*n* = 12 clusters; *n* = 212 Shedders) a wait list control cohort served as a comparator (*n* = 3 clusters; *n* = 89 Shedders) and these were a subset of the second cohort (*n* = 9 clusters, *n* = 209 Shedders). Fourteen clusters were in urban areas and 8 were in rural areas across counties; Kildare (in Ireland’s mid-east region with a population of ca. 222, 504), Waterford (in Ireland’s south-east region with a population of ca. 116,176), Limerick (in Ireland’s south-east region with a population of ca. 194,899) and Louth (in Ireland’s mid-east region with a population of 128, 884) [48]. Participants were recruited for Phase 1 across Waterford and Kildare in March to May 2019 and Limerick and Louth in September to December 2019. Participants for Phase 2 will be recruited from September to December 2021 (recruitment was postponed until this date due to COVID-19 restrictions).

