#### Evaluating the effectiveness of SFL- data analysis

Questionnaire data is analysed using Statistical Packages for the Social Sciences (SPSS V 24). Descriptive statistics for each variable are calculated to inform participant characteristics. Intervention effect on health and wellbeing outcomes are determined by comparing the change scores from baseline to 3, 6 and 12 months, comparing data using inferential tests to identify significant differences set at *p* = 0.05. Analysis of subgroups based on criteria such as; Shed size location and timing of the intervention, will also be performed to identify significant differences in intervention effect between groups. Outcome data obtained from all participants are included in the data analysis, regardless of adherence to SFL. The intervention effects will be assessed at 3, 6 and 12 months based on those who completed follow-up at these time points. Assuming a worst case scenario for absentees i.e. that absentees failed to achieve a significant improvement in core health outcomes (physical activity, diet, mental wellbeing, subjective wellbeing, social capital and help-seeking), these worst- case scenario analyses will reflect the intention to treat principle. The numbers who achieved significant improvement at 3, 6 and 12 months will be presented as a percentage of those who were tested at these follow-up points. For the initial intervention effect worst-case scenario, the numbers who achieved significant improvements at 3 months will be presented as a percentage of those who were tested at baseline. The worst-case scenario for maintenance of this initial intervention effect will present the numbers who achieved significant improvements at 6 and 12 months as a percentage of those who were tested at the 3 month follow-up. Observed success rates will be compared between the intervention and comparison group in waiting using Chi-Square analysis.

A hybrid analytic approach of inductive and deductive analysis is applied to the participant transcripts. This means that whilst implementation frameworks are applied to inform implementation outcomes, the analysis process will remain open to findings that may emerge outside of those pre-set domains to allow assessment of intervention effect. In these circumstances, inter-rater reliability is used to cross-check coding strategies and interpretations are negotiated to agree on a ‘master’ code list.

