#### Evaluating the implementation of SFL -data analysis

Data pertaining to SFL participation (attendance records, self-reported attendance, numbers who participated versus numbers eligible) are triangulated to assess penetration. Cost-effectiveness is being determined by comparing the costs (direct and indirect) of SFL to its benefits which will be captured as the impact on quality-adjusted life-years (QALYs) derived from the short form-6D algorithm. Qualitative data are analysed using a framework-driven approach, applying the CFIR to inform implementation outcomes. Focus groups and interviews will be transcribed and, as per recommendations by the National Cancer Institute’s White Paper on qualitative research in implementation science, a hybrid approach of thematic deductive and inductive analysis will be used to inform implementation outcomes [44]. This means that whilst the CFIR domains will be applied to inform implementation outcomes, the analysis process will remain open to findings that may emerge outside of those pre-set domains. A constant comparison process previously outlined will again be applied.

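### No untreated group remains at 12 months and none is described at 6, so the later change scores are uncontrolled before-after change, not intervention effects

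*Protocol article*

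**What the plan says.** All references are to the protocol article.

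- **Delivery** (Part 1, Overview): "the SFL 10-week intervention was implemented on a phased basis across two cohorts comprising two counties in each cohort". Both Phase 1 cohorts receive the programme.
- **Comparator** (Participants and sampling): "Whilst delivery occurred in the first cohort", "a wait list control cohort served as a comparator (*n* = 3 clusters; *n* = 89 Shedders", and "these were a subset of the second cohort". Cohort 1 has 12 clusters and 212 men; cohort 2 has 9 clusters and 209 men.
- **Dates** (same section): "Participants were recruited for Phase 1 across Waterford and Kildare in March to May 2019 and Limerick and Louth in September to December 2019".
- **Follow-up** (effectiveness data collection): cohort 2 has its own 6- and 12-month follow-up, done by telephone under COVID-19 restrictions.
- **Effect** (effectiveness data analysis): the effect is determined from change scores between baseline and each follow-up. The section continues: "The intervention effects will be assessed at 3, 6 and 12 months based on those who completed follow-up at these time points". It uses the word maintenance only for the worst-case percentages at 6 and 12 months. The one between-group test, a Chi-square against the group in waiting, has no time point.
- **Label** (Table 2): the study is called a pragmatic controlled trial, with questionnaires at baseline, 3, 6 and 12 months.
- **Cost-effectiveness** (implementation data collection and analysis): the same four questionnaires inform cost, and the analysis works by "comparing the costs (direct and indirect) of SFL to its benefits which will be captured as the impact on quality-adjusted life-years". Neither a comparator nor a horizon is given.
- **Limitations**: non-randomisation and self-report are named. The loss of the comparator after the waiting period is not.

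**The concern.** A wait-list design gives a controlled contrast only for as long as the wait list waits. After that, a change score in treated men is a before-after difference. It contains whatever SFL did plus everything else that moved the outcome: regression to the mean, season, repeated questioning and, for cohort 2, the pandemic and a change of questionnaire mode. Physical activity, loneliness, wellbeing and social capital could plausibly shift for several of these reasons.

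The stated aim is impact up to 12 months, and the findings are meant to inform policy makers, service providers and decisions on scale-up. If 6- and 12-month change is reported under the name of intervention effect, those readers will take it as controlled evidence. A cost per QALY that draws on the later questionnaires would carry the same weakness.

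**Working it through.** **1. Membership.** The plan's own total reproduces: 212 + 209 = 421 men. If the 89 were a separate group the total would be 212 + 209 + 89 = 510. The 89 are therefore inside the 209, as the text says, and are 89/421 = 21% of all treated men. (The cluster counts do not quite add up: 12 + 9 = 21 against the stated 22. This does not affect the point.)

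**2. Calendar.** Assume baseline is at recruitment, that Limerick and Louth are cohort 2, and that cohort 2's SFL starts at recruitment.

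| | Baseline | 3 months | 6 months | 12 months |
|---|---|---|---|---|
| Cohort 1 | Mar–May 2019 | Jun–Aug 2019 | Sep–Nov 2019 | Mar–May 2020 |
| Cohort 2 | Sep–Dec 2019 | Dec 2019–Mar 2020 | Mar–Jun 2020 | Sep–Dec 2020 |

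Ten weeks from the cohort 2 recruitment window (1 September to 31 December 2019) ends between 10 November 2019 and 10 March 2020.

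**3. Untreated men planned for comparison at each of cohort 1's time points.**

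- About 3 months: 89 men (3 clusters) against 212 (12 clusters).
- 6 months: none described. Cohort 1's window overlaps cohort 2 recruitment, so some wait-list men may not yet have started, but the article describes no untreated assessment of them at that point.
- 12 months: 0 of 421. Cohort 2 is by then at its own post-baseline follow-up.

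**4. A date that needs explaining.** Cohort 1's 3-month window (June to August 2019) closes before cohort 2 recruitment opens (September 2019). A concurrent wait-list comparison is possible only if the three wait-list clusters were enrolled and measured earlier than the stated dates. The article does not say so.

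**5. How large a drift would look like an effect?** This is an illustration only. From the document: design effect 2.4 and 20% dropout, so 421 × 0.8 = 337 followed. Assumed: SD of change = 0.9 baseline SD, and that the design effect, taken from the sample-size calculation, also applies to within-man change.

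- SE = 0.9 × √(2.4/337) = 0.076 SD.
- Drift 0.1 SD: z = 0.1/0.076 = 1.3, not significant.
- Drift 0.2 SD: z = 0.2/0.076 = 2.6, significant.
- Break-even at two-sided 0.05: 1.96 × 0.076 = 0.15 SD.

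**The case against.** The study says openly that it is pragmatic and non-randomised. The analysis section also partly separates the time points: its worst-case percentages distinguish an initial effect at 3 months from maintenance at 6 and 12, and the only between-group test is against men in waiting. On that reading no controlled 12-month contrast is promised, and the rest is loose wording. This stands in part. However, maintenance covers only those percentages. The section still applies the term intervention effects to all three time points, and no further analysis detail could supply an untreated 12-month group.

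A reader might also infer four stronger things that the article does not support:

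- *That the gap is as certain at 6 months as at 12.* At 6 months it is inferred, because the wait list's start date is not given.
- *That the plan claims QALY gains at 12 months.* It gives no QALY horizon. The only link is that the 6- and 12-month questionnaires are among those informing cost.
- *That the 89 men will sit on both sides of the Chi-square test.* Participants and sampling points to 212 against 89, which do not overlap. Since the test has no time point and its intervention side is not defined as cohort 1, the wording permits the overlap but does not prescribe it.
- *That ordinary drift is bound to be declared significant.* The z range above includes non-significant values and rests on assumed inputs.

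**Conclusion.** The point holds. A controlled effect can be estimated only over the waiting period, about 3 months, and even that depends on the wait list having been measured alongside cohort 1, which the stated dates leave open. At 12 months the absence of an untreated group follows directly from the text: 0 of 421. At 6 months no untreated assessment is described. Calling the later change scores intervention effects is wrong as written, and the Limitations section does not warn of it. The size of any resulting error is unknown; the drift calculation shows only that about 0.15 SD would reach significance under the stated assumptions. Double membership of the 89 men is a risk of the wording, and the cost-effectiveness concern applies only to figures that use data beyond the waiting period.

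**What to change.** 1. Reconcile the cohort 2 recruitment dates with the wait list's role as a concurrent comparator, and state when the wait-list men were measured and when they started SFL.
2. State that the controlled effect is estimated only over the waiting period (about 3 months), as cohort 1 (212 men) against the wait list (89 men). Use only wait-list data collected before their SFL starts, so that the groups are disjoint, and allow for clustering by Shed. Give the between-group success-rate comparison this time point.
3. Label all 6- and 12-month results as within-group change or maintenance, and add the loss of the comparator to the Limitations.
4. Present any QALY or cost-effectiveness figure that uses data beyond the waiting period as an uncontrolled before-after scenario.
5. If the wait-list men's later data are pooled, use a mixed model with a time-varying SFL-exposure term and random effects for both man and Shed. This handles the men's dual role; it does not create an untreated group at 12 months.

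The cost is mainly wording and some analysis specification, with no new data. The downside is a weaker statement about 6 to 12 months.

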Sheds are a community-based, grassroots movement which originated in Australia and have since grown exponentially in Ireland. Sheds have long been recognised not just as a suitable setting in which to actively promote and engage men in health but also as being imbued with inherent and organic health promoting qualities [26]. Sheds are autonomous grass roots spaces which are non-structured and informal, varying in size and resources. Sheds offer a safe and familiar environment for Shed members (‘Shedders’) and foster a sense of social support, belonging and camaraderie, through developing new skills, shared projects, activities, goals and decision making [27]. All of these factors have been linked with enhancing the health and wellbeing of the men who attend with social support, in particular, being frequently reported as a key enabler of men’s help-seeking [28]. The enhanced sense of belongingness that is attributed to the non-conventional setting of Sheds increases their appeal to typically HTR men [29–31]. This is also the case in more recent research which suggests that the Sheds have a protective effect against loneliness [32]. The inherent health promoting qualities of Sheds therefore present a strong foundation upon which to build structured health promotion programmes. Moreover, drawing from a rich source of past interventions that utilised strengths-based and gender-specific approaches, the Men’s Sheds setting is well-positioned to deliver tailored, targeted health promotion initiatives to what has been traditionally regarded as an inaccessible of HTR cohort of men [33]. Nevertheless, it is also critically important that such endeavours enrich rather than erode the ethos of the Shed environment, which means that programmes need to be pragmatically evaluated with Shedders at the centre of decision making [33, 34]. Conventional wisdom dictates that health interventions need to be delivered systematically, to be context free, with strict inclusion criteria. However, Sheds are not just highly variable, autonomous, non-structured spaces; these are the very characteristics that define the essence of Sheds and which need to be respected in order to uphold the integrity and ethos of the Sheds. The challenge therefore is to develop a pragmatic delivery design that can operate within an organic, non-structured space, where contextual factors vary, where attendance can be sporadic, and where there is no compulsion on members to undertake any activity.

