#### Evaluating the effectiveness of SFL- data collection

Questionnaires are administered to participants by a research team member trained in data collection procedures to ensure standardised measurement and questionnaire administration. Questionnaires are administered one-to-one in the Sheds setting to account for potential literacy issues, prevent respondent burn-out, limit missing data and build rapport and trust between the researchers and Shedders. To also minimise missing data, participants will be contacted by the IMSA in the days before the research team visit the Sheds to perform data collection. Due to the informal nature of the Sheds, absence of data for a participant does will not necessarily indicate dropout from SFL. During 6 and 12 month follow-up in Phase 1, Cohort 2 were experiencing COVID-19 restrictions and therefore questionnaires were administered via phone in order to promote participant retention and complete follow-up. The questionnaire was designed via a consultation process with stakeholders involved in the design and delivery of SFL with a view to optimising acceptability for SFL participants and also SFL providers who were interested in evaluating their individual components of SFL. Participant demographics are recorded at baseline and include date of birth, living arrangements, educational attainment, employment status relationship and ethnicity. Participants are also asked how long they had been a Shed member and how often they attend the Shed. Core health and wellbeing outcomes measured at all-time points up to 12 months consist of; subjective wellbeing, help-seeking, physical activity, mental wellbeing, diet and cooking skills, social capital and self-efficacy. Participants are also asked how often they seek information about their health.

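### Mean change is assessed only in men seen at each visit although intermittent absence is expected; a mixed model on all available assessments rests on a weaker assumption and needs an MNAR sensitivity analysis beside it

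*Protocol article*

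**What the plan says.** The section *Evaluating the effectiveness of SFL – data analysis* defines the effect by "comparing the change scores from baseline to 3, 6 and 12 months", with "significant differences set at *p* = 0.05", and fixes whose data count: "The intervention effects will be assessed at 3, 6 and 12 months based on those who completed follow-up at these time points".

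A neighbouring sentence says "Outcome data obtained from all participants are included in the data analysis, regardless of adherence to SFL". That keeps men who were measured but did not follow the programme. It says nothing about men who were not measured.

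Absentees are handled in one place only. For the percentages who improved, an absentee is counted as not improved, and "these worst- case scenario analyses will reflect the intention to treat principle". The companion observed percentages are "presented as a percentage of those who were tested at these follow-up points". The worst-case denominator is men tested at baseline for the 3-month result, and men tested at 3 months for the 6- and 12-month results. No equivalent is described for mean change.

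Two other sections bear on this. The background section on Men's Sheds says that "attendance can be sporadic". The data collection section says that "absence of data for a participant does will not necessarily indicate dropout from SFL".

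**The concern.** The article expects a pattern in which a man may miss one visit and be seen at another. A separate change-score comparison at each visit makes no use of his other assessments when estimating the visit he missed. It is unbiased only if absence is unrelated to change.

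Two things are at stake. First, the estimated mean change at a visit can be wrong if those present differ from those absent. Second, the 3-, 6- and 12-month results come from different sets of men, so a comparison across time mixes change within men with change in who was seen. That matters because the article wants to speak about maintenance up to 12 months.

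This is a choice that the article states, not a detail it leaves open.

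**Working it through.** **1. The loss figure.** *Participants and sampling* gives 106 participants, a design effect of about 2.4 and 20% dropout.
- 106 × 2.4 = 254.4, rounded up to 255.
- 255 × 1.2 = 306, the stated total.

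The figures reproduce. The 20% is the only loss rate given. It is a dropout allowance, so absence at any one visit could be higher.

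**2. Error in one arm's mean.** Let *p* be the proportion absent, and δ the mean change in those present minus that in those absent. The completer mean minus the full-cohort mean is *p* × δ. With *p* = 0.20 and δ = 0.25 to 0.5 SD (assumed):
- 0.20 × 0.25 = 0.05 SD
- 0.20 × 0.50 = 0.10 SD

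The sign follows δ, which the article does not inform.

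**3. Error in the controlled contrast.** This is *p*₁δ₁ − *p*₀δ₀ for the intervention and wait-list groups. If absence is the same in both, it is zero. The 0.05 to 0.10 SD carries over in full only if absence is selective in one group alone.

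**4. Success rates, for comparison.** Assume 50% success in those seen and 25% in absentees. The full-cohort rate is 0.8 × 50% + 0.2 × 25% = 45%. The plan would report 50% (observed) and 0.8 × 50% = 40% (worst case), which bracket 45%. Mean change has no such bracket.

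**5. Does a mixed model help?** A simulation compared visit-wise completers with a likelihood-based repeated-measures model (unstructured covariance) on all available data. It used 212 and 89 men as in *Participants and sampling*, and 300 runs per scenario. The assumptions were SD 1, a true effect of 0.4 SD, within-person correlation 0.3, 0.5 or 0.7, about 18 to 24% missing per visit in the intervention arm, no clustering, and comparator data at baseline and 3 months only. Under MAR (absence depends on the last observed value) and MNAR (absence depends on the unseen current value), that dependence was placed in the intervention arm only.

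Bias in SD units, for correlation 0.3 / 0.5 / 0.7:

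| Absence | Estimate | Completers | Mixed model |
|---|---|---|---|
| MCAR | 3-month contrast | −0.014 / 0.003 / 0.004 | −0.011 / 0.004 / 0.005 |
| MAR | 3-month contrast | −0.123 / −0.090 / −0.048 | 0.007 / 0.002 / 0.005 |
| MAR | 12-month within-arm change | −0.029 / −0.019 / −0.013 | 0.001 / 0.000 / −0.001 |
| MNAR | 3-month contrast | 0.135 / 0.083 / 0.049 | 0.163 / 0.116 / 0.075 |
| MNAR | 12-month within-arm change | 0.130 / 0.083 / 0.053 | 0.161 / 0.117 / 0.078 |

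The largest simulation error is about 0.176/√300 = 0.01. The variance ratio (completers over mixed model) ran from 0.98 to 1.16, mostly 1.02 to 1.10.

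**The case against.** The strongest reply is that the remedy does not match the most natural worry. If absentees do worse for reasons not visible in recorded data, absence is MNAR. There the mixed model was slightly more biased than completers. Where it did help, under MAR, completers understated the effect. This stands: a reader might infer that the completer analysis overstates benefit and that a mixed model is simply less biased, but neither holds in general.

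Other parts of the reply also stand:
- **Data are not thrown away.** A man absent at 3 months but seen at 6 still counts at 6. His later assessment is only unused for the visit he missed.
- **Later visits add little to the controlled contrast.** The wait-list men are a subset of the second cohort, which itself receives the programme. I therefore take the contrast to rest on baseline and 3 months; the article does not state how long the comparator was held.
- **Absence is mitigated.** Participants are contacted before data-collection visits. Cohort 2 (209 of 421 men) was followed by phone at 6 and 12 months, so attendance at the Shed on the day does not decide who is seen there. It cannot be inferred that apparent maintenance is an artefact of selective attendance.
- **A Shed random effect is fragile** with 3 comparator clusters.
- **No share of the target effect can be given.** The article states no effect size behind the 106, and a one-arm error should not be divided by a between-group effect.

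The reply that this is only missing detail does not stand. The article names the analysis set and gives absentees a rule for success rates but none for mean change.

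**Conclusion.** The point holds in a limited form. Mean change at 3, 6 and 12 months is tied to men seen at each visit, in a setting where the article expects intermittent absence. The stated worst case does not reach those results. They are unbiased only if absence is unrelated to change, and the three visits describe different sets of men.

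The possible error is 0.05 to 0.10 SD in one arm's mean at 20% loss. It rests on an assumed difference of 0.25 to 0.5 SD, is of unknown sign, and is smaller in the contrast if both groups lose men alike. A mixed model is valid under the weaker MAR assumption. Under the assumed inputs it cut a 3-month completer bias of about 0.05 to 0.12 SD to 0.01 SD or less. It offers no bias advantage under MCAR and does not cure MNAR, so a sensitivity analysis is part of the remedy. The case for the change is the weaker assumption; the precision gain is minor.

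**What to change.** Make the effect analysis for each mean-change outcome a repeated-measures linear mixed model on all available assessments, including men with baseline only. Specify:
- time, group and group-by-time, with the controlled contrast at 3 months only, and 6 and 12 months reported as within-cohort change;
- the baseline characteristics already recorded;
- participant and Shed effects, with a small-sample correction because the comparator has only 3 clusters.

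Keep the visit-wise completer analysis as supportive. Add a delta-adjusted (MNAR) sensitivity analysis for the mean-change outcomes, for example shifting absentees' values over 0 to 0.5 SD, in one group and in both.

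The cost is some extra analysis work in the SPSS software already named, and no new data. *Dissemination* describes the Phase 1 interim analysis as still to be performed, so as written the change can still be specified. The price is reliance on missing at random, which the delta adjustment examines but cannot remove. The gain in precision is small, with variance about 2 to 10% lower under the assumed inputs.
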